### Adverse Event Reporting and Harms

As for safety evaluations, all adverse events will be reported and evaluated. Adverse events refer to any unfavorable change in clinical symptoms, laboratory data, or disease temporally associated with probiotics used in this trial, regardless of whether it is considered to be related to the trial product. However, unfavorable clinical symptoms such as constipation, which could be considered due to maternal physiological changes, are not treated as an adverse event. When an adverse event occurs, patients will receive appropriate treatment, and the cost will be supported by the national health insurance. All serious adverse events that could be assumed to be caused by probiotics used in this trial must be reported and investigated to the Clinical Research Review Board of Toyama University Hospital. In addition, the information will be shared with all investigators.

### Data Analysis

#### Sample Size Calculation

Based on the previously reported rate of recurrent sPTD at <37 weeks of gestation of 22.3% in Japan [6], we considered a clinically significant reduction in the relative risk to be 30% (risk ratio=0.7). Assuming the effect of the probiotics corresponds to a risk ratio of 0.7 (with the rates under the null hypothesis being 0.223 and under the alternative hypothesis being 0.156) and using a 1-sided test with a significance level of .025 and a power of 80%, the required sample size was calculated to be 298 participants. We considered a withdrawal rate of 10% based on the incidence of miscarriage at <22 weeks of gestation [29] and a dropout rate of 5% and, thus, set the required sample size to 345 participants.

#### Statistical Analysis

The efficacy analysis set consists of all patients enrolled in this trial except for patients who will not be treated with the protocol treatment, whose data will not be collected after the protocol treatment starts, who are designated to be ineligible after enrollment, or in whom pregnancy was terminated before 21 weeks of gestation for any reason.

The safety analysis set consists of patients who will be treated with the protocol treatment at least once. Frequencies and percentages are calculated for discrete variables, and summary statistics (mean, standard deviation, minimum, median, or maximum) are calculated for continuous variables. As the primary analysis, we will conduct a binomial test on the rate of recurrent sPTD at <37 weeks of gestation.

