## Methods

### Trial Design

The Prevention of Recurrent Spontaneous Preterm Delivery by Probiotics (PPP) trial is designed as a prospective, single-arm, nonblinded, multicenter clinical trial to confirm the prevention of sPTD by oral probiotics in pregnant women with a history of sPTD. In Japan, 31 hospitals are participating, and the trial is scheduled to run from April 1, 2021, to March 31, 2025 (registration period was from June 1, 2021, to March 31, 2024.) The design of the trial is summarized in Figure 1. This trial will be performed according to the ethical principles originating from the Declaration of Helsinki and the Clinical Trial Act.

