#### Exclusion Criteria

The exclusion criteria included pregnant women with a history of indicated preterm birth, such as abruptio placentae, gestational diabetes mellitus, pregnancy-induced hypertension, eclampsia, HELLP (Hemolysis, Elevated Liver Enzymes, and Low Platelets) syndrome, pulmonary embolism, cerebral hemorrhage, pulmonary edema, acute fatty liver of pregnancy, placenta previa, fetal growth restriction (≤–2.0 SD), oligohydramnios, polyhydramnios, fetal diseases with chromosomal abnormalities, fetuses with multiple malformations, fetal edema, fetal dysfunction, and pregnant women with histories of sPTD for a multiple pregnancy. In addition, pregnant women with a multiple pregnancy (singleton cases after multifetal pregnancy reduction or another fetal death are also excluded), a severe physical disability, with a history of serious hypersensitivity or anaphylactic reactions caused by probiotics (including lactomin, *C. butyricum*, and amylolytic bacillus), using a medical drug or supplement including *Clostridium* spp. within 2 weeks before enrollment, with a history of cervical conization, with uterine malformation, with cervical polyps and massive genital bleeding before 10 weeks of gestation, with subchorionic hematoma and massive genital bleeding at the time of obtaining informed consent, who regularly use steroids, with diabetes mellitus, with autoimmune disease, diagnosed or treated for malignant disease at the time of informed consent (cases in which malignant disease has been completely cured may be included), with fetal morphological abnormalities at the time of informed consent, currently participating in other clinical trials or those who previously participated in a clinical trial and for whom at least 1 month has not passed since the last dose of the study drug was taken, or classified as inapplicable for this trial by the investigators are excluded.

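### The primary efficacy set drops women declared ineligible after enrolment, with no limit to pre-dose facts or to decisions made without the delivery outcome

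*Protocol article*

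**What the plan says.** The Statistical Analysis section builds the efficacy set from all enrolled women and then removes four groups: those never treated, those "whose data will not be collected after the protocol treatment starts", those "who are designated to be ineligible after enrollment", and those "in whom pregnancy was terminated before 21 weeks of gestation for any reason". The primary analysis follows in the same section: "we will conduct a binomial test on the rate of recurrent sPTD at <37 weeks of gestation".

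Other parts of the article bear on how the third removal would work:

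- Trial Design: the study is "designed as a prospective, single-arm, nonblinded, multicenter clinical trial".
- Recruitment Setting: women are registered once eligibility has been confirmed, so a finding of ineligibility after enrolment revises an earlier decision.
- Exclusion Criteria: some criteria are tied to the time of consent (fetal morphological abnormality, malignant disease). Others carry no date (uterine malformation, autoimmune disease, history of indicated preterm birth). The list ends with an open judgement: women "classified as inapplicable for this trial by the investigators are excluded".
- Data Management: after a preterm delivery, further information, including placental histology, is recorded for 4 weeks. After a term delivery only basic neonatal data are recorded. The local principal investigator enters the data.

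**The concern.** The rule as written lets a treated woman leave the primary set after her delivery outcome is known. Late discovery of a disqualifying fact is more likely when someone is looking for the cause of an early delivery, and the article itself plans closer data collection after preterm births. The open judgement criterion adds room for discretion. No control arm shares the exclusions, so any association between removal and outcome passes straight into the one proportion being tested. If removed women had sPTD more often than those kept, the analysed rate falls for reasons unrelated to the probiotic, and the one-sided test rejects too often.

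**Working it through.** **Inputs.** From Sample Size Calculation: the design is stated "with the rates under the null hypothesis being 0.223 and under the alternative hypothesis being 0.156", one-sided alpha 0.025, power 80%, 298 evaluable women, 10% withdrawal, 5% dropout, 345 enrolled. The number of ineligibility exclusions and the sPTD rate among those removed are not given, so both are assumptions below.

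**The plan's own figure.** Take an exact lower-tail binomial test, where success means X ≤ c and c is the largest count with P(X ≤ c | n, 0.223) ≤ 0.025. Checked up to n = 344, 298 is the smallest n from which exact power at 0.156 stays at or above 80%; n = 297 gives 79.7%. At n = 298, c = 52, the exact size is 2.37% and power is 83.2%. Inflation gives 298 × 1.10 × 1.05 = 344.2, rounded up to 345. The sample size reproduces and is not in question.

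**Analysed number used here.** 345 × 0.90 × 0.95 = 294.98, so n = 295. There c = 51 and the exact type I error is P(X ≤ 51 | 295, 0.223) = 2.1%.

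**Worst case: every removed woman had sPTD.** Remove k events from numerator and denominator. The test on 295 − k women succeeds when X − k ≤ c(295 − k), so type I error is P(X ≤ c(295 − k) + k | 295, 0.223).

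| k removed | women left | c | X in 295 must be ≤ | type I error |
|---|---|---|---|---|
| 0 | 295 | 51 | 51 | 2.1% |
| 3 | 292 | 50 | 53 | 4.0% |
| 5 | 290 | 50 | 55 | 7.3% |
| 8 | 287 | 49 | 57 | 12.2% |

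**Milder cases: 8 removed, a fraction q of whom had sPTD.** The overall true rate stays at 22.3%, which is 295 × 0.223 = 65.785 expected events. The rate among the 287 left is (65.785 − 8q)/287, and the test still needs X ≤ 49.

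| q | rate in those left | type I error |
|---|---|---|
| 22.3% (unrelated to outcome) | 22.3% | 1.8% |
| 40% | (65.785 − 3.2)/287 = 21.8% | 2.8% |
| 50% | (65.785 − 4.0)/287 = 21.5% | 3.6% |

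The 1.8% lies below 2.1% only because the exact test moves in steps as n changes.

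**Fragility of one result.** P(X ≤ 53 | 295, 0.223) = .040, not significant. Without two of those events, P(X ≤ 51 | 293, 0.223) = .024, significant. At the planned 298, 53/298 (P=.033) becomes 51/296 (P=.019).

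**Unknown outcomes, a separate question.** Suppose 16 of 310 women (about 5% of 345 × 0.90) have no delivery outcome and all are counted as events. The boundary for 310 is 54, so at most 54 − 16 = 38 events are allowed among the other 294. Power at 15.6% is then about 12%, against about 82% when the 16 are left out. Counting all as events is thus a severe bound and unsuitable as the primary rule.

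**The case against.** The strongest reply is that a condensed article commonly leaves the timing and logging of eligibility decisions to the full protocol or SAP, and that removing untreated, no-data and ineligible women is a common modified full analysis set. A safeguard may exist that is not shown. That is fair as to procedure. But the article does state the rule for its primary set, and the rule as stated permits removal after delivery; the criticism is of that wording.

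Second, most eligibility criteria are facts that predate treatment, and nothing in the article says the judgement criterion may be used after delivery. This stands as a limit. The exposure is confined to late discovery of undated criteria and to the open criterion. A fetal abnormality first found later is not a ground for ineligibility as written, because that criterion is tied to consent.

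Third, the authors show awareness of the hazard. In the Discussion they considered excluding women with long antibiotic use, noted that most of them have sPTD, and did not exclude them. This speaks for their intent, but it does not extend to the ineligibility rule.

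Fourth, the women with no data after treatment start are not removed because of a known outcome. This is correct: they are a missing-data problem and need a different check.

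**Conclusion.** The point holds as a statement of risk. The primary set can be changed on grounds related to outcome, in a design with no blinding and no comparator to absorb the effect. For 8 removals from 295 women with a true rate of 22.3%, type I error ranges from about 1.8% (unrelated to outcome), through 2.8% to 3.6% (40% to 50% with sPTD), to 12.2% (all with sPTD). Moderate selection of that size is a modest problem; the larger figure is a worst case. Even so, two removed events can reverse a result close to the boundary. All of this rests on assumed numbers and rates of removal.

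A reader might infer three stronger things that the article does not support:

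- That the bias can run only towards success. Downward is the more plausible direction, but removing women at lower risk would raise the rate.
- That the 22.3% benchmark passed through no comparable filter. The article says only that it comes from a perinatal registration database. Its exclusions are in a cited source that is not at hand.
- That 12.2% is the trial's expected error rate, or that such removals have occurred. The article gives no evidence of either.

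**What to change.** Before analysis, amend the efficacy-set definition:

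1. Exclude for ineligibility only when a criterion was not met on facts that existed before the first dose, with each decision made and logged by people unaware of the delivery outcome. Otherwise keep all treated women who reach the plan's gestational cut-off in the primary set. The cut-off itself is a separate matter and is left as the plan has it.
2. As a sensitivity analysis, repeat the binomial test in all treated women who reach the cut-off, with no ineligibility exclusions.
3. As a separate missing-data check, report the test with unknown delivery outcomes counted once as events and once as non-events.
4. Report the number of ineligibility exclusions, with the reason and delivery outcome for each.

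The cost is a change of wording, a short decision log and two or three extra runs of the same test. The downside is that a few ineligible women may stay in the primary set. The Results section says that 345 women are registered and that data collection was expected to run to October 2024, so the change affects neither recruitment nor sample size.

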### Study Participants

#### Recruitment Setting

We will recruit pregnant women who meet all the inclusion criteria and do not have any of the listed exclusion criteria. In Japan, most women visit an obstetrical clinic between 5 weeks and 8 weeks of gestation. After confirming the eligibility criteria, we will register pregnant women. In this trial, a history of sPTD is defined as preterm delivery by labor pains, clinical chorioamnionitis, intrauterine infection, or histological chorioamnionitis diagnosed after preterm delivery, with or without obstetrical complications. Informed consent will be obtained from pregnant women prior to their registration. Pregnant women can review the details of this trial on the Japan Registry of Clinical Trial.

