### Study Procedures

The trial schedule is shown in Figure 2. All registered pregnant women will receive oral probiotics. The probiotics used are already available drugs including *C. butyricum* (10 mg/tablet), *Enterococcus faecium* (2 mg/tablet), and *Bacillus subtilis* (10 mg/tablet), because the probiotics containing *C. butyricum* alone are not commercially available in Japan. Probiotics are started from 10 weeks to 14 weeks and stopped at 36 weeks 6 days of gestation, late miscarriage, or sPTD. The maximum duration of administration is 188 days.

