**Figure 3 figure3:**
[figure not shown]
The Bristol Stool Form Scale.

**Table 1 table1:** The Constipation Scoring System (total of 30 points possible).

Items evaluated	Points				
	0	1	2	3	4
Frequency of bowel movements	1-2 times per 1-2 days	2 times per week	Once per week	Less than once per week	Less than once per month
Painful evacuation effort	Never	Rarely	Sometimes	Usually	Always
Feeling of an incomplete evacuation	Never	Rarely	Sometimes	Usually	Always
Abdominal pain	Never	Rarely	Sometimes	Usually	Always
Time spent on the toilet to defecate (minutes)	<5	5-9	10-19	20-29	≥30
Type of assistance	No assistance	Stimulative laxatives	Digital assistance or enema	—^a^	—
Unsuccessful attempts to evacuate per 24 hours	0	1-3	4-6	7-9	≥10
Duration of constipation (years)	<1	1-5	6-10	11-20	≥21

^a^Not applicable.

In this trial, any treatment to prevent late miscarriage or sPTD, such as progesterone (17-alpha-hydroxyprogesterone caproate, which is used at a dosage of 125 mg and covered by the national health insurance system in Japan but is not used to prevent sPTD in the first trimester), cerclage, tocolysis, and antibiotics, could be used because there is no evidence to support their prevention of sPTD. The previously reported rate of recurrent sPTD of 22.3% in Japan [6] is presumed to be the result of these treatments.

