### Endpoints

The primary endpoint is the rate of recurrent sPTD at <37 weeks of gestation. The secondary endpoints are the rate of sPTD at <34 weeks of gestation, the rate of recurrent sPTD at <28 weeks of gestation, the proportion of stillbirth, constipation (using the BFS and CSS), the ratio of intestinal *Clostridium* spp. (as measured using next-generation sequencing [NGS]), and bacterial vaginosis (using the Nugent score). In cases of sPTD, histological chorioamnionitis, or funisitis, neonatal prognosis (gestational weeks at delivery, birth weight, hospitalization in the neonatal intensive care unit [NICU], neonatal death, respiratory distress syndrome, PVL, BPD, IVH, and NEC) will be evaluated.

In this trial, to analyze the composition of the microbiota (using NGS), a stool collection brush and storage tube (Fujifilm WAKO Pure Chemicals) containing DMSO-EDTA salt solution buffer [26] was prepared, and 2 tubes were delivered to each participant. Pretreatment feces were collected in the tubes by each participant and stored under cool conditions. Posttreatment (22±2 weeks of gestation) feces were also collected. These tubes were compiled at ReLife Inc at a temperature <4°C, then transported to the Kyoto Institute of Nutrition and Pathology for analyses of the microbiota composition.

Fecal DNA was extracted using a commercial kit (QuickGene DNA tissue kit, KURABO) as described elsewhere [27]. The procedure for metagenomic 16S rRNA sequencing using Miseq (Illumina) was the same as that previously described [28]. The processing of sequencing data, including quality filtering, chimera checks, operational taxonomic unit definitions, and taxonomy assignments, was performed using QIIME1.9.1, USEARCH, and UCHIME in the same manner as previously described [28]. Alpha-diversity metrics (the Chao1 or Shannon index) were calculated using QIIME1.9.1 software. To calculate the distances between samples, beta-diversity was estimated using the UniFrac metric and visualized using a principal coordinate analysis.

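### The efficacy set cuts at 21 weeks and the withdrawal allowance at 22 weeks, so a spontaneous loss in week 21 stays in the primary denominator with its scoring open to two readings

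*Protocol article*

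**What the plan says.** Two sections of the protocol article decide who reaches the primary binomial test, and they use different gestational weeks.

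- **Statistical Analysis** leaves out of the efficacy set, among others, women "in whom pregnancy was terminated before 21 weeks of gestation for any reason". A pregnancy that ends at 21w0d or later is kept.
- **Sample Size Calculation**: "We considered a withdrawal rate of 10% based on the incidence of miscarriage at <22 weeks of gestation". Here everything up to 21w6d is miscarriage and is expected to leave the analysable cohort.

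On scoring, the article gives the following.

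- **Endpoints**: "The primary endpoint is the rate of recurrent sPTD at <37 weeks of gestation". There is an upper limit and no lower one.
- **Recruitment Setting** has the only definition of sPTD. It concerns obstetric history, rests on cause ("a history of sPTD is defined as preterm delivery by labor pains, clinical chorioamnionitis, intrauterine infection, or histological chorioamnionitis"), and has no lower week.
- **Study Procedures** names late miscarriage and sPTD side by side as different outcomes. Probiotics are "stopped at 36 weeks 6 days of gestation, late miscarriage, or sPTD", and the paragraph after Table 1 allows "any treatment to prevent late miscarriage or sPTD". Neither place gives the week that divides the two.
- **Data Management** likewise lists earlier miscarriage and earlier sPTD as separate items of history.

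**The concern.** The two cut-offs disagree about one group: women with a spontaneous loss between 21w0d and 21w6d. The sample size treats them as withdrawals, and the analysis set keeps them. Once kept, they must be scored, and the article supports two answers. If miscarriage and sPTD are different things and a loss below 22 weeks is a miscarriage, the woman is a non-event in the denominator and lowers the observed rate. If every spontaneous delivery below 37 weeks counts, she is an event.

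The design gives this some weight. The trial is single-arm and nonblinded, and the rate is tested against a fixed 22.3%. No control arm carries the same ambiguity, so the scoring choice enters the result directly and would be made by people who know the outcomes. The same open week affects the secondary sPTD rates below 34 and below 28 weeks.

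**Working it through.** **Inputs.** From Sample Size Calculation: null rate 0.223, alternative 0.156, one-sided level 0.025, power 80%, 298 evaluable, 345 enrolled, 10% withdrawal, 5% dropout. From Statistical Analysis: a binomial test. Assumed: k, the number of spontaneous losses at 21w0d to 21w6d among the 298. The article does not give k. It may be 0, and 1 to 3 is shown for illustration.

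**Step 1: the plan's own figures.** The exact lower-tail binomial test reproduces 298. It is the smallest n from which exact power stays at or above 80% for all larger n up to the 344 searched (n = 297 gives 79.7%). At n = 298 the trial succeeds with at most 52 events: P(X ≤ 52 | 298, 0.223) = 0.0237 and P(X ≤ 52 | 298, 0.156) = 0.832. The enrolment figure follows as 298 × 1.10 × 1.05 = 344.2, rounded up to 345. The mismatch of weeks is not an arithmetic error and does not alter either number.

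**Step 2: losses outside the stated rates.** Suppose 0.223 and 0.156 describe only the other 298 − k women, with the success rule still at most 52 events.

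- Kept as non-events: size = P(X ≤ 52 | 298 − k, 0.223).
- Added as events: power = P(X ≤ 52 − k | 298 − k, 0.156).

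| k | Size, kept as non-events | Power, added as events |
|---|---|---|
| 0 | 2.37% | 83.2% |
| 1 | 2.54% | 79.7% |
| 2 | 2.72% | 75.9% |
| 3 | 2.91% | 71.6% |

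**Step 3: losses already inside the stated rates.** Now let the overall rate p (0.223 or 0.156) include these women, scored in the trial as in the source of the rate.

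- As events: the others have rate (298p − k)/(298 − k), and success is at most 52 − k events among them. For k = 1 to 3, power is 83.4% to 83.9% and size stays below 2.37%.
- As non-events: the others have rate 298p/(298 − k), and success is at most 52 events. Size is 2.37% to 2.36% and power 83.2%.

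There is then no harm. This holds only while the trial and the source score these women the same way.

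**Step 4: one common cut-off.** If week-21 losses are excluded and the critical count is recomputed, size stays at or below 2.5%. Power is 79.7% at n = 297 (at most 51 events), 80.5% at n = 296 and 81.2% at n = 295. With one such woman, excluding her gives the same 79.7% as scoring her as an event. The case for alignment is therefore clarity, not recovered power.

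**The case against.** A planning allowance taken from a published miscarriage incidence need not use the same week as an analysis-set rule, and it does not classify outcomes. The exclusion may also be loose wording for losses through 21w6d, which would agree with the sample size. The plain reading of an endpoint below 37 weeks in a set that starts at 21w0d is that a spontaneous week-21 delivery is an event. Finally, an article condenses a full protocol, and a SAP may give the lower limit of sPTD.

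Much of this stands. A reader might infer that the plan scores a late pregnancy loss as a treatment success. The article does not say so: that reading comes from joining its vocabulary in one section to its miscarriage limit in another, and the literal endpoint points the other way. A reader might also infer that the 2.5% level is breached or that power is lost. Both need at least one week-21 loss and need those losses to lie outside the stated rates, and neither condition can be checked from the article. Nor can the effect on the rate below 28 weeks be sized, because both the losses and the events would have to be assumed.

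What does not fall away is that the article itself states two different weeks. An unseen SAP could settle the scoring, but not the disagreement between these two sentences. If the exclusion was meant to run through 21w6d, it is misworded and needs the same correction.

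**Conclusion.** The point holds as a conflict between two stated cut-offs, one gestational week apart, that leaves a small group in the primary denominator with two supportable scorings. It does not show an error in the sample size, and it does not establish an inflated error rate. Under the assumption of 1 to 3 such losses outside the stated rates, size is 2.54% to 2.91% if they are non-events, and power at 0.156 is 79.7% to 71.6% if they are events. With none, or with losses already inside the stated rates and scored alike, the effect is little or nothing. Which case applies depends on how the source of the 22.3% counted week-21 losses, which the article does not report. Severity: minor.

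**What to change.** Before database lock:

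1. Use one gestational boundary in Sample Size Calculation and Statistical Analysis: pregnancy ended before 22 weeks 0 days, unless the source of the 22.3% uses another lower limit, in which case match that limit.
2. Apply the same lower limit to the primary endpoint and to the sPTD rates below 34 and below 28 weeks.
3. Report losses below the boundary separately, and do not count them as non-events.

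The cost is a short wording change and a check of the benchmark's definition. No new data are needed, because the existing exclusion already requires the week in which each pregnancy ended. The planned 298 and 345 stand. The downside is a denominator that may be smaller by a few women.
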